#### 4.a.2. Exclusion Criteria

1. Veteran recently continued to engage in a maladaptive pattern of alcohol/substance use and/or abuse (as defined in protocol).
2. Veteran has used potent CYP3A4 inhibitors (fluconazole, ketoconazole, itraconazole, erythromycin, rifampin) and inducers within five half-lives prior to randomization.
3. Veteran is taking simvastatin, lovastatin, fentanyl, pimozide, bupropion, nefazodone, dihydroergotamine, ergotamine, quinidine, sirolimus, tacrolimus, or clarithromycin, cyclosporine, St. John's Wort, diltiazem, verapamil, propranolol, alprazolam, carvedilol or some anticonvulsants (phenytoin, phenobarbital, or carbamazepine) within five half-lives prior to randomization.
4. Veteran is taking oral corticosteroids within five half-lives prior to randomization.
5. Veteran should be free of a major medical illness and medical condition that contraindicate the administration of mifepristone. These include but are not limited to:
  - a. Veteran has a history of adrenal insufficiency or a low plasma cortisol level at screening (a.m. level less than 5 mcg/dl or a p.m. level of less than 3 mcg/dl.)
  - b. Veteran has a history of severe traumatic brain injury, a history of a stroke, or another neurological illness or injury likely to impact cognitive functioning.
  - c. Veteran has diabetes mellitus, an endocrinopathy, or another major medical illness.

- d. Veteran has a history of cardiovascular disease including a history of angina, myocardial infarction or other evidence of coronary artery disease, or congestive heart failure
  - e. Veteran has prolonged QTc interval >450 msec on ECG at screening.
  - f. Veteran has hypokalemia at screening (defined as potassium level < 3.5 mEq/L)
  - g. Veteran has a history of hepato-biliary disease or an AST, ALT greater than 2X the ULN.
  - h. Veteran has a history of renal disease or an estimated GFR of < 60 ml/min.
6. Veteran has a lifetime diagnosis of schizophrenia, schizoaffective disorder, or type I bipolar disorder.
  7. Veteran has a history of attempted suicide within the previous two years or active suicidal ideation within the past month as assessed by the Columbia-Suicide Severity Rating Scale (C-SSRS).
  8. Veteran is currently receiving specialized trauma-focused psychotherapy, such as prolonged exposure therapy and cognitive processing therapy.
  9. Veteran is not willing to use effective means of birth control during the study.
  10. Veteran has a history of allergic reaction to mifepristone.
  11. Veteran is found to be unsuitable for study participation at the discretion of the site investigator for any reason.

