## 4. Work Proposed

### 4.a. Overview

90 eligible male veterans with chronic PTSD will be randomly assigned to treatment with 600 mg/day mifepristone or placebo for one week and assessed for clinical outcomes at one and three months follow-up. Eligibility will be based on the inclusion and exclusion criteria which are enumerated below and in the Human Participants section. The inclusion and exclusion criteria were selected in order to include as representative a sample as possible while also addressing safety concerns. Veterans who are actively suicidal as assessed by the Columbia-Suicide Severity Rating Scale (C-SSRS) or who have attempted suicide within the past two years will be excluded. (If suicidality is identified, the necessary steps will be taken to ensure the appropriate clinical care is provided, and the local suicide prevention policies implemented.) Veterans with adrenal insufficiency will be excluded, as will veterans with other major medical or neurological illnesses, as they may be at increased risk of developing adverse events. Veterans with renal disease/impairment, hepatic disease/impairment, cardiac illness (e.g. coronary vascular disease, congestive heart failure), or hypokalemia at screening will also be excluded. Since mifepristone use can prolong the QTc interval in a dose-related manner, veterans with a prolonged QTc interval, defined as >450 msec, on the ECG at screening will be excluded. To evaluate QTc prolongation post-mifepristone treatment, an ECG will also be performed at both the 3 day follow up visit (visit 1.5) and 1 week follow-up visit (week 1, visit 2).

Participants on potent CYP3A4 inhibitors (fluconazole, ketoconazole, itraconazole, erythromycin, rifampin) and some anticonvulsants (e.g., phenytoin, phenobarbital, and carbamazepine) will be excluded since these medications impact the metabolism of mifepristone (see Risk/Benefit Assessment for details). Due to an increased risk of adverse drug reactions, veterans taking simvastatin, lovastatin, fentanyl, pimozone, bupropion, nefazodone, dihydroergotamine, ergotamine, quinidine, sirolimus, carvedilol, propranolol, diltiazem, verapamil, alprazolam, or tacrolimus will also be excluded. Since the impact of mifepristone on the male reproductive system has not been extensively studied, only veterans willing to use effective means of birth control for up to 90 days after mifepristone ingestion will be eligible; this will cover the critical period of fetal development.

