Blood samples will be obtained for the assessment of basal pre-treatment neuroendocrine activity (i.e., plasma cortisol and ACTH levels). Veterans will be called the day before their scheduled visit and asked to fast from midnight until after the blood draw. 10 ml of blood will be drawn by routine venipuncture for the determination of basal plasma cortisol and ACTH. Blood samples for hormonal analysis are collected into tubes containing ethylenediaminetetraacetic acid (EDTA), spun immediately in a cold centrifuge, and frozen for subsequent analysis. They will be shipped in batches to the Core Lab. Since observed changes in ACTH and cortisol could effectively break the blind if performed in the local hospital lab, samples will be assayed at the Clinical Neuroscience Lab at the James J. Peters VA Medical Center (Director: [name]).

Clinical assessments to be administered at the baseline visit include the CAPS, Beck Depression Inventory (BDI) (Beck et al., 1996), PTSD Checklist (PCL Military Version) (Weathers et al., 1996), National Institute on Alcohol Abuse and Alcoholism (NIAAA) Quantity and Frequency Questionnaire, State-Trait Anger Expression Inventory (STAXI) (Spielberger et al., 1988), and the Pittsburgh Sleep Quality Index (PSQI) (Buysse et al., 1989).

To address quantity and frequency of alcohol use within the last 30 days, participants will be asked to answer three NIAAA questions. This information will be obtained at baseline, 1 week follow-up, 1 month follow-up, and 3 month follow-up. Participants will be asked to report how many days per week or days per month they had at least one alcoholic beverage (defined as 1 can or bottle of beer, 1 glass of wine, 1 can or bottle of wine cooler, 1 cocktail, or 1 shot of liquor) in the last 30 days, how many drinks they consumed on average on the days in which they drank, and how many times during the last 30 days they consumed 5 or more drinks on one occasion. This measure will be used as a potential covariate to examine the effects of alcohol use on clinical outcomes.

Since grapefruit juice may increase the amount of mifepristone in blood and increase the chance of adverse events, participants will be instructed to not drink grapefruit juice while they are taking study medication.

Participants will be randomized at the end of the baseline visit, and will receive study medication.

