#### 4.d.2. *Randomization Procedures*

Patients determined to be eligible and willing to participate in the study will be randomly assigned to 600 mg mifepristone or placebo using a web-based randomization system with a telephone call randomization system as back-up. The clinical research assistant at the participating facility will be required to sign into this password-protected site. The clinical research assistant will enter the patient study number and will be asked to answer a few questions about eligibility in order to complete the randomization procedure. If met, the website will select the first unused entry from the pre-specified list of random treatment assignments for the particular site and then assign a randomization number, which will be used to order the double-blind treatment prescription from the study site pharmacy. The randomization lists are stored on a secure server at Hines CSP Central Study File labeled "restricted access". A copy of appropriately executed and completed consent and HIPAA authorization documents must be on file at the Hines CSPCC within 24 hours of randomization, preferably before the patient is randomized. If the internet server is down during normal business hours, the clinical research assistant can telephone the Hines CSPCC to randomize a patient.

If a participant hasn't received the study drug on the day the participant is randomized, site coordinators should make every effort to ensure the participant receives the drug within 3 days post randomization, follows the directions on how to take the drug correctly, and that no study prohibited concomitant medications are used during this period. Should the study drug assignment program be down on any business day, site coordinators will contact the Albuquerque Pharmacy Center to request an emergency manual assignment.

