#### 4.e. Treatment Algorithm

Medication treatment will be for one week duration, and randomized participants will be given a seven-day supply of medication. Three weeks after the pulse treatment, the participant will undergo clinical reassessment. If participants develop an AE or as SAE that is deemed unsafe by the PI, they will be taken off treatment immediately but will be followed per protocol. The research team does not anticipate the occurrence of study-related SAEs, as the dose levels used in this trial have been used before in other studies without SAEs. In our pilot study of mifepristone in PTSD, no veterans were taken off treatment.

Both the active study medication and its matching placebo will be donated by Corcept Therapeutics.

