#### 4.f. Follow-Up Assessments

The study physician will assume the psychiatric care of the participant for the duration of the study. A research flag in the electronic medical record will be established for each patient to alert other providers to the veteran's participation in the study and of the need to refer psychiatric matters to the study physician. The patients other providers will also be informed of important clinical events by personal communication and/or through their inclusion as additional co-signers on research-related notes made in the electronic medical record.

As outlined in Table 2, the veteran will be assessed in person 48 to 72 hours after taking the first dose of the study drug. An ECG, vital signs (pulse, blood pressure, temperature), and medical labs (complete blood cell count, fasting glucose, cortisol, and electrolytes) will be taken. Any symptoms and changes in concomitant medications will also be reviewed. The checkup is intended for safety reasons. Follow ups will occur immediately after the pulsed treatment (one week follow-up), at one month follow-up, and at three month follow-up. At each of these three visits, the participant will be assessed for safety (adverse event reporting, vital

signs and weight, C-SSRS interview), PTSD and psychiatric status (CAPS and self-report measures), and concomitant medication use. In addition, blood will be drawn for medical labs (complete blood cell count, fasting glucose, and electrolytes) and neuroendocrine assessment (plasma cortisol and ACTH) at the day 3, one week and one month follow-up visits; an ECG will also be performed at the one week follow-up visit. Refer to figure 3 for a timeline of study visits.

In order to quantify the amount of co-therapy the participant receives during the study, the psychosocial treatment schedule provided in the Longitudinal Interval Follow-up Evaluation (LIFE) study will be used. With this instrument we will collect data about the types of therapy the veteran has received. Specifically, we will collect information about the number of sessions per week that the patient has had of the following types of therapy: individual, group, family, medication session, or self-help. The information will be collected at one month intervals (1 month follow-up (week 4, visit 4); 2 month follow-up telephone check-in (week 8, visit 6); 3 month follow-up (week 12, visit 8).

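### Exclusion 9 ties contraception to the study period, while the section 4.a overview ties it to 90 days after the drug; the two should be aligned

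*Protocol*

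**What the plan says.** The section 4.a overview notes that mifepristone's effect on the male reproductive system has had limited study. It then says that "only veterans willing to use effective means of birth control for up to 90 days after mifepristone ingestion will be eligible", and gives the reason: "this will cover the critical period of fetal development". It does not say whether the 90 days run from the first or the last dose.

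Section 4.a.2 restates the condition as exclusion 9: "Veteran is not willing to use effective means of birth control during the study". There is no number of days, and the period is attached to the study instead of to exposure.

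On which text decides eligibility, the overview says: "Eligibility will be based on the inclusion and exclusion criteria which are enumerated below and in the Human Participants section". The Human Participants section it mentions is not among the pages available.

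**The concern.** A contraception period justified by fetal safety should run from exposure to the drug. The overview does this; exclusion 9 does not. The numbered list is what a site would naturally check at screening, and it carries the looser rule. For a man who stays to the last visit the two periods nearly coincide. They separate for a man who leaves the study, because a period defined by participation may be taken to end when participation ends, while one defined by ingestion does not. What is at stake is a small gap in a safety precaution. No statistical quantity depends on it.

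**Working it through.** The plan gives no figure of its own to reproduce, so the check is calendar arithmetic on the two wordings.

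**Inputs**
- Day 0: section 4.c says "Participants will be randomized at the end of the baseline visit, and will receive study medication".
- Possible delay: section 4.d.2 says "site coordinators should make every effort to ensure the participant receives the drug within 3 days post randomization", so the first dose may fall on day 3.
- Dosing days: the drug description gives 14 tablets, two each evening, which is 14 / 2 = 7 daily doses. They fall on days 0 to 6, or days 3 to 9 with the delay.
- Last visit: section 4.f lists "3 month follow-up (week 12, visit 8"), and 12 x 7 = day 84. No window is stated for this visit, so day 84 is nominal.
- Alternative end: section 4.g calls this a three-month study. Read as 13 weeks, that is 13 x 7 = day 91.
- Assumption: 90 days is the full intended period. The start point is open, so both first and last dose are shown.

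**Formula:** shortfall = (dose day + 90) - day the study ends.

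**Completers, study ends on day 84**
- First dose, no delay: 0 + 90 - 84 = 6 days
- Last dose, no delay: 6 + 90 - 84 = 12 days
- First dose, 3-day delay: 3 + 90 - 84 = 9 days
- Last dose, 3-day delay: 9 + 90 - 84 = 15 days

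As a share of the period, this is 6/90 = 7% to 15/90 = 17%.

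**Completers, study ends on day 91**
- First dose, no delay: 0 + 90 - 91 = -1, so no shortfall
- Last dose, no delay: 6 + 90 - 91 = 5 days
- First dose, 3-day delay: 3 + 90 - 91 = 2 days
- Last dose, 3-day delay: 9 + 90 - 91 = 8 days

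**Early leavers.** Suppose that the study is read as ending on a man's exit day x, and that he took all seven doses without delay. The shortfall is then 90 - x from the first dose and 96 - x from the last. Exit on day 28 gives 62 to 68 days; exit on day 56 gives 34 to 40. These are illustrations of that reading only. Stopping the drug for an adverse event is not leaving the study: section 4.e says such men "they will be taken off treatment immediately but will be followed per protocol", so the early-exit calculation does not apply to them.

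**The case against.** The strongest reply is that the overview sentence is itself an eligibility condition, tied to ingestion. A man who would refuse contraception after an early exit fails that condition whatever exclusion 9 says. The numbered list is also plainly shorthand in other places: item 1 leaves its definition of recent substance misuse to the protocol text, item 5b leaves the definition of severe brain injury to section 4.a, and item 7 leaves its suicidal-ideation threshold to section 4.i. And since 'up to' 90 days can be a ceiling, the two sentences do not contradict each other literally.

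Most of this stands, and it rules out three stronger readings that a reader might infer.
- *That a man who leaves early is committed to nothing.* The documents do not support this, because the overview condition applies as well. The pages that would show what participants are told are not available.
- *That early leavers have a fixed shortfall of two to three months.* Nothing defines the period in exclusion 9 as ending at personal withdrawal. The size also depends on the end point chosen. For exit in the treatment week, taking the assessment that section 4.h requests three weeks after the last dose as the end gives 63 to 69 days; taking day 7 as the end gives 83 to 89. The number of such men is unknown. The planned 20% attrition (0.20 x 45 = 9 per arm if equal) covers all losses over the trial, not exits in that week.
- *That the study ends at week 4, because the schedule labels that visit the study endpoint.* Sections 4.f and 4.g, with a week 12 visit and a three-month study, make week 12 the better reading.

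What the reply does not remove is the mismatch itself. Where item 1 points the reader to the fuller text, exclusion 9 does not; it substitutes a different anchor. The stated fetal-safety purpose fits 90 days as a full period better than as a ceiling, so the phrase 'up to' is also worth correcting.

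**Conclusion.** The point holds as a minor safety inconsistency between two statements of one rule in section 4.a. It is not the absence of a contraception commitment. Its size rests on two assumptions: that sites screen on exclusion 9 alone, and that 90 days is the full period. Under both, completers fall about 6 to 15 days short at nominal day 84, or 0 to 8 days if three months means 91 days. Early leavers could fall further short, but only if the study is read as ending at withdrawal, and neither their number nor a single figure for their gap can be taken from the protocol. The finding concerns the wording of these two sentences and nothing in the statistical design.

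**What to change.** Reword exclusion 9 along these lines: *not willing to use effective contraception through 90 days after the last dose of study drug, whether or not he remains in the study*. Put the same period into the section 4.a overview in place of the 'up to' phrase. The sponsor's clinicians should confirm the start point; the last dose is the safer choice.

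The cost is one sentence and one phrase, with no added visit or procedure. Participants commit for slightly longer: to about day 6 + 90 = 96, or day 9 + 90 = 99 with the 3-day delay, which is 12 to 15 days past the nominal week 12 visit. Sample size, endpoint and analysis do not change.

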#### 4.b. Recruitment Process and Informed Consent

Patients with a presumptive diagnosis of PTSD will be recruited through direct contacts during visits to outpatient mental health and primary care clinics by informing mental health care providers and other clinical providers about the study so as to elicit direct referrals and, having obtained Institutional Review Board (IRB) approval for a partial HIPAA waiver, by direct contacts after chart reviews and physician consultations for patients with PTSD. Before contacting potentially eligible patients, the study team will review the clinical history in the electronic patient chart at the site to investigate inclusion and exclusion criteria. For those eligibility items not found in the chart or found but out-of-date, the study team will determine what information needs to be obtained during the pre-consent and post-consent screening visits. Once it is mutually agreed upon that the patient is eligible for trial participation, that the strategy within the protocol is clinically acceptable, and that the primary physician is agreeable to the patient being contacted for possible study participation, patients will be contacted. The method for this contact, (i.e. by phone or letter and with pre-established oral or written scripts) will require approval by the governing IRB. If patients from any of the above contact sources agree to be evaluated, they will have an initial visit with the study team. During this visit, the study team will ensure the patient fits the study's inclusion criteria and does not have a reason to be excluded. The study will be explained to them and the Informed Consent Form (ICF) will be reviewed in its entirety. At that time, or after further consideration of the study by the patient and his physician and family, the patient will be asked to sign the ICF and HIPAA authorization, copies of which will be given to them. The investigators consider this consent process to be an ongoing process maintained throughout the study to provide patients with a continued understanding of the protocol, their participation, and their rights as human research participants. Remuneration is provided for time and expenses (\$25 for screening/medical evaluation; \$50 per visit for a total of four visits (baseline, one week follow-up, one month follow-up, three month follow-up)), but is not so high as to coerce an individual to participate who would not otherwise participate (see Human Subjects section for more information on participant remuneration). After the signed ICF is obtained, additional screening procedures covered in the ICF will be conducted prior to randomization.

Participant recruitment will be the responsibility of the clinical research staff and local principal investigator (PI). The study staff will educate their clinical colleagues regarding this study opportunity. Veterans with a confirmed or presumptive diagnosis of PTSD will be identified in VA outpatient clinics (e.g. PTSD, mental health, or primary care clinics). Mental health professionals at the VA will be alerted about the study and the study staff will maintain frequent communication with them so that potentially eligible veterans will be referred to the study. Veterans expressing an interest in learning more will be referred to study personnel for preliminary screening and informed consent. Informed consent will be obtained by the study PI or by an IRB-approved delegate after a screening interview, but prior to the initiation of any study procedures. As the initial step in the consent process, the study will be explained to the veteran in detail and the consent

form will be read to the veteran in its entirety by the PI or an IRB-approved delegate. The participant will be fully informed about all aspects of this study and will be given ample time for clarification and to have his questions answered. The veteran will be able to bring the consent form home and can discuss the study with his physician, family members, or others prior to making a decision. A de-identified log will be kept of all veterans who are screened for the study, even if they are ineligible, in order to characterize the larger population from which the sample was drawn and the reasons veterans were found to be ineligible.

